## Methods

### Overall design

The intervention mixed methods design involves a stepped-wedge cluster randomized controlled trial testing the outcomes of training in recovery-oriented practice, together with an embedded qualitative study to identify the contextual enablers and challenges to implementing recovery-oriented practice within primary care settings. Eighteen general practices and community health centers were randomly allocated to one of two steps (9 months apart) to start an intervention comprising general practitioner training in the delivery of recovery-oriented practice. Data collection consists of cross-sectional surveys collected from patients of participating general practitioners at three time points: baseline, and again at the end of Steps 1 and 2 (see Fig. 1). A mixed methods design was chosen for a number of reasons, including that it would produce richer and more complete findings than that based on either the qualitative or quantitative approach alone. Combining these approaches can further explain and enhance the integrity of the project outcomes, so that a mixed methods design may assist with project credibility, particularly when multiple stakeholders are involved such as in the PULSAR project [28]. The use of qualitative and quantitative methods were integrated at different stages of the intervention trial [27]. Initially, qualitative methods were used in an exploratory manner to identify potential barriers to recovery-oriented training within primary care settings, and to inform the intervention design. Subsequently, quantitative methods are being used to then measure the effectiveness of the intervention. Following the intervention trial, qualitative methods will be used in an explanatory manner to gain a more nuanced understanding of GP experiences of implementing recovery-oriented practices and patient experiences of these practices [28]. Quantitative and qualitative data are collected from patient participants, but only qualitative data are collected from GP participants.

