Additional measures are: Participant Demographic Record and the General-practice-Users Perceived-need Inventory (GUPI) [48]. As well, a section in the survey is designed to gain an understanding of any financial burden of illness as well as the participants’ use of health services. These health economic and service utilization questions, which contain both study-specific items and questions adapted from the 2007 Australian National Survey of Mental Health and Wellbeing [49], include information on the participants’ job status, income, consultations with health professionals, medications being taken, admissions to hospital, and any time away from usual roles because of illness. Participants are advised that if they cannot answer a question precisely, then to provide a best estimate and that there are no ‘right’ or ‘wrong’ answers. Finally, where specific consent is provided, information related to diagnosis, mental health status and current medication is also collected from GP medical records.

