
## Statistical analyses

The recovery-oriented practice training intervention for primary care will be evaluated at the patient level by examining the surveys of adult patients who consult the participating GPs for mental health issues. The main evaluation plan is to examine the cross-sectional surveys returned by patients during three data collection periods: baseline, Step 1, and Step 2 (see Fig. 1).

The planned data collection schedule depends on the training intervention being delivered at each cluster in the scheduled month (see Fig. 1). As training delays in some clusters are expected, the following two main analysis approaches are planned to compare the post-intervention and control (pre-intervention) periods:Study planned dataset, which will use data collected from patients during the planned six-month periods centered on the midpoints of February 2015, August 2015 and November 2015 (see Fig. 1). Other data collected outside of these timespans are considered a protocol violation and are excluded from this dataset.Per-protocol all data dataset, which will use all available data time-stamped from date of intervention received at the cluster, as outlined in Table 3.

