### Main analysis plan

Descriptive statistics will be used to summarize the characteristics of the patient-level variables and the GP clinics (clusters), see Table 2. Cluster-level variables are those used in the stratified randomization, which are four types of organizational variations, plus the intervention status of the cluster and the time since (or before) the intervention. The intraclass correlation coefficient (ICC) will be calculated and reported.

**Table 2 Tab2:** Individual and cluster-level variables available for multivariable analysis

Variable	Description
*Individual level*	
Demographics	
Sex	Sex of patient.
Age	Age of patient at survey completion date.
Country of birth	Country of birth of patient.
Ethnicity	Ethnic or cultural group that the patient identifies with.
Main language	Main language spoken at home.
Marital Status	Marital status of patient.
Living situation	Current living situation of patient.
Education	Education level of the patient.
Health Economics	
Mental health medications	Medications for mental health taken regularly by the patient.
Employment	Current working status of the patient.
Income	Usual weekly income of patient, after tax, from all sources of employment.
Days out of role	Number of days in the past month that the patient was totally or partly unable to carry out normal activities because of mental health problems.
Days absent from work	Number of days in the past month that the patient was absent from work due to illness or disability, and due to mental health problems.
Hospitalizations	Number of hospital admissions for physical problems and for mental health problems, including number of nights in total and reasons for most recent admissions.
Consultations with health professionals	Number and length of consultations with health professionals for physical health and mental health problems.
GUPI	The General-Practice Users’ Perceived-need Inventory is a one-page instrument developed to assess participants’ estimation of their needs for mental health care and the meeting of those needs.
*Cluster level*	
Cluster group	Allocated to receive the intervention at either Step 1 or Step 2.
Intervention status (0/1)	A lag time of six months is anticipated until intervention effects are possible. The intervention status variable indicates that this lag time has passed.
Dosage (%)	Intervention dosage.

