Time since intervention	All patient surveys are time-stamped in relation to the time the intervention was received at the cluster. Time value of “0” is given for the plus/minus three months from date of training; “1” for four-to-six months post training; “2” for seven-to-nine months post training, etc. Time value of “-1” for four-to-six months before training; “-2” for seven-to-nine months before training, etc.
Time	Study month that survey was completed: “0” = December 2014, “1” = January 2015, etc.
*Cluster level stratification variables*	
Clinic type	Privately owned general practice vs community health center.
GP clinic size	GP equivalent full time (EFT) size greater than 5 (yes/no).
Clinic location	Local government area location: Dandenong, Casey, Cardinia, other.
Specialist focus clinic	A specialist focus clinic (yes/no) was determined by more than 10% of the practice patients belonging to any of the following groups: a. people with HIV/AIDS b. people with enduring and serious mental illness (e.g., schizophrenia, bipolar disorder) c. people with permanent physical disabilities d. people with addictions e. homeless people f. transient/seasonal populations g. people living in poverty h. Aboriginal peoples i. recent immigrants (six months or less) j. people from cultural minorities k. people with sports injuries l. other

The primary analysis will examine the patient-level QPR scores (continuous data) at baseline, nine months (Step 1), and 18 months (Step 2), using a linear mixed-effects model. The model will include intervention status and time as fixed effects and clusters and patients as random effects. Both univariate and multivariable models will be developed based on baseline patient and cluster-level variables considered statistically significant (*p <* 0.10) or clinically important (e.g., age, sex), see Table 2, and included in the model as fixed. This will include the intervention dosage variable described earlier. Model fit will be examined by comparing AIC values.

Secondary analyses will examine the patient-level data of the INSPIRE, WEMWBS, and K10. Similar to the primary analysis, we will use linear mixed-effects models to compare the intervention and control periods (pre-intervention) for continuous outcomes and generalized linear mixed-effects models for binary outcomes.

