### Data collection and management

Table 3 outlines the data collected at each time point for participating GPs and patients. Patient participant data is being collected by the returned paper surveys or online surveys at three time points: baseline (months 4–6), Step 1 (months 16–18) and Step 2 (months 28–30), as displayed in Fig. 1. Both modes of survey completion are provided to offer flexible participation options. The estimated completion time for each round of surveys is approximately 45 min.

**Table 3 Tab3:** Schedule of enrolment, interventions, and assessments

	Time points			
Project events		T0	T1	T2
Intervention adaptation	X			
GP enrolment				
Eligibility screen	X			
Informed consent	X			
Randomization	X			
GP training intervention				
Year 1 clusters		X		
Year 2 clusters			X	
GP PALS				
Year 1 clusters		X	X	X
Year 2 clusters			X	X
Patient recruitment				
Eligibility screen by GP		X	X	X
Survey packs provided to eligible patients via GPs		X	X	X
Informed consent		X	X	X
Patient quantitative assessment				
Demographics		X	X	X
QPR		X	X	X
WEMWBS		X	X	X
INSPIRE		X	X	X
K10		X	X	X
Health economic items		X	X	X
GUPI		X	X	X
GP qualitative assessment				
Informed consent			X	X
Individual interview			X	
Individual interview/focus group				X
Patient qualitative assessment				
Informed consent			X	X
Individual interview			X	
Individual interview/focus group				X

The online survey option collects participant-entered data directly from Qualtrics online survey software. Qualtrics securely collects participant responses within a secure back-end spreadsheet that is only accessible by the researchers via password protected files.

If patient participants consent to allowing the researchers to access their routinely collected medical records, additional information will be extracted from these files with the assistance of the participating GP/s in each cluster site, including information about diagnosis and mental health status and medication details relating to mental health issues.

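### The multivariable QPR models may adjust for patient variables recorded after training, so their intervention coefficient need not be the total training effect

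*Protocol article*

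**What the plan says.** **The rule.** The Main analysis plan describes a linear mixed model for the QPR, with intervention status and time as fixed effects and clusters and patients as random effects. It then plans both univariate and multivariable models, and "multivariable models will be developed based on baseline patient and cluster-level variables considered statistically significant" at p<0.10, or clinically important, are added as fixed effects. Age and sex are the examples of clinical importance. AIC is used to compare fit.

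**The candidates.** These come from Table 2, titled "Individual and cluster-level variables available for multivariable analysis". Besides demographics it lists mental health medications, employment, income, days absent from work, hospitalizations and consultations. It also lists days out of role ("Number of days in the past month that the patient was totally or partly unable to carry out normal activities") and the GUPI, "developed to assess participants’ estimation of their needs for mental health care and the meeting of those needs". Nothing separates variables that training could change from those it could not.

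**The timing.** Under Overall design, "Data collection consists of cross-sectional surveys collected from patients of participating general practitioners at three time points". The Statistical analyses section repeats this: "The main evaluation plan is to examine the cross-sectional surveys returned by patients during three data collection periods: baseline, Step 1, and Step 2". Table 3 (Data collection and management) marks demographics, health economic items and GUPI at T0, T1 and T2, the same points as the QPR. The Measures section places the service-use items inside the patient questionnaire.

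**The concern.** A covariate that training can change is safe in a model for the training effect only if it was measured before training. Here it would be measured before training in control cells and after training in intervention cells. Conditioning on it then takes out of the intervention coefficient whatever part of the effect runs through it or moves with it. The Aims and objectives ask whether patients of trained practices report greater personal recovery, which is the total effect. A coefficient that holds met need or days out of role constant answers a different question.

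Some of these variables are also what the trial sets out to evaluate. Research question 3 concerns perceived need, which the GUPI measures. Research question 4 concerns service costs, which the Economic evaluation section builds from medications, hospital and service contacts, and days off work.

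**Working it through.** **1. When are the covariates recorded?** Every respondent in the baseline wave, and every Step 1 respondent in the later group, answers before the cluster's scheduled training. Step 1 respondents in the earlier group, and all Step 2 respondents, answer after it. Two readings of baseline are possible:
- *The patient's own baseline value.* None is planned for Step 1 and Step 2 respondents.
- *Variables selected in baseline-wave data.* The values then entered for later respondents are still post-training.

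Neither makes these items pre-training covariates. Days out of role and days absent have past-month recall. Table 2 gives no recall window for admissions and consultations, so those could partly predate training.

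**2. Which candidates are affected?**
- *Trial outcome:* GUPI (research question 3).
- *Cost inputs:* medications, hospitalizations, consultations, days absent (research question 4, Economic evaluation).
- *Plausibly affected, but not named in either:* days out of role.
- *Not affected:* age, sex, country of birth, ethnicity, main language, education and the stratification factors.

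**3. Yardstick from the plan's inputs.** Sample size targets gives SD 16, ICC 0.05, power 0.80, alpha 0.05 (taken as two-sided), two steps and three time points. The 600 patients are 20 × 30, but no target difference is stated, so 600 cannot be reproduced as a power result. With I clusters, T = 3 periods, cluster variance τ² and cluster-period mean variance σ²/m = s², the cross-sectional stepped-wedge variance is

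Var = I·s²·(s² + Tτ²) / [(IU − W)s² + (U² + ITU − TW − IV)τ²],

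where U is the number of treated cluster-periods, W the sum of squared period totals and V the sum of squared cluster totals. The detectable difference is (1.960 + 0.842) × SE:
- 20 clusters × 10 per period: SE 2.472, difference 6.93 points (0.43 SD).
- 18 clusters, 30 GPs × 10 patients (16.7 per cluster-period): SE 2.068, difference 5.79 points (0.36 SD).

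**4. Size of the distortion.** The documents give no covariate associations, so all inputs here are assumed. For one covariate that training shifts by d SD, with slope b on QPR (SD per SD),

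adjusted effect = total effect − b·d.

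*Illustration A.* Total effect 8 points (0.5 SD), d = 0.2 in the favourable direction, b = 0.5. The loss is 0.5 × 0.2 × 16 = 1.6 points, leaving 6.4 (20% lower). A simulation of 200 trials (18 clusters, 17 patients per cluster-period) gave 7.99 points without the covariate (simulation SE 0.15) and 6.41 with it (0.13). The covariate passed p<0.10 in all 200. For d from 0.1 to 0.3 and b from 0.3 to 0.5, the loss is 0.48 to 2.4 points: 6–30% of a 0.5 SD effect, or 10–50% of a 0.3 SD effect.

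*Illustration B.* Total effect 0.40 SD (6.4 points). The covariate has correlation ρ with the within-cluster part of QPR, so b = ρ√0.95.
- ρ = 0.5, d = 0.3: 0.40 − 0.5 × 0.975 × 0.3 = 0.254 SD (4.1 points, 37% lower).
- With 17 per cluster-period the SE is 0.128 SD. Unadjusted power is Φ(0.40/0.128 − 1.96) = 0.88. Adjusted power is Φ(0.254/(0.128 × √0.75) − 1.96) = 0.63, even after crediting the smaller residual variance.
- ρ from 0.3 to 0.7 and d from 0.1 to 0.4: the loss runs from 0.3 × 0.975 × 0.1 / 0.40 = 7% to 0.7 × 0.975 × 0.4 / 0.40 = 68%.

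*Opposite sign.* If training raises need or service use by 0.2 SD and that goes with lower QPR (ρ = −0.3), the adjusted effect is 0.40 + 0.3 × 0.975 × 0.2 = 0.46 SD, about 15% too large.

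**The case against.** **The adjusted model is not declared primary.** A reader might infer that the primary QPR result will come from a model containing these variables. The text does not say so. The core model is described without patient covariates, and a univariate version, free of this problem, is planned. This objection stands. What remains is that the article does not say which model supplies the primary estimate.

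**Entry of particular variables is not certain.** The article does not say which test the p<0.10 refers to, gives no correlations with QPR, and lists Table 2 items only as available. This also stands. Still, if the test is association with QPR, days out of role and GUPI are likely entrants, and comparison by AIC favours strong concurrent correlates whether or not training affects them.

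**The direction is open.** A reader might infer that effective training would necessarily look weaker or null. The documents do not support that. The training covers treatment planning, which could raise consultations, medication or perceived need, and the bias would then be upward. Nor does the article say that training is meant to change hospitalizations, medication or days out of role; its stated purpose is personal recovery.

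**Dropping medication has a cost.** GPs who know their training status organize recruitment in each wave, under a 7:3 quota defined partly by antidepressant and antipsychotic prescribing. Case mix may differ between control and trained periods, and medication is a natural proxy for it. This stands, and it argues for a labelled secondary model rather than a ban.

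**Conclusion.** The concern holds in a limited form. The stated rule calls variables baseline that, for trained-period respondents, are recorded after training, and it leaves outcomes and cost inputs among the candidates. If such variables are selected, the adjusted coefficient is not the total training effect, and it may err in either direction. This is a fault in what the article states, not detail left to an analysis plan.

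The size cannot be determined from the documents. Under the assumed shifts and associations, attenuation runs from about 6% to 68% of the effect. The 0.5 to 2.4 points of Illustration A compare with a detectable difference of about 6 to 7 points. The 37% loss and the fall in power from 88% to 63% describe one assumed case, not a forecast. The conclusion does not touch fixed demographics, the stratification factors or the univariate model. The dosage covariate is a separate matter.

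**What to change.** In the Main analysis plan and Table 2:

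1. Name the model that gives the primary estimate: intervention status, time and cluster effects, adjusted only for the stratification factors and for patient characteristics training cannot plausibly change (age, sex, country of birth, ethnicity, main language, education).
2. Remove GUPI, days out of role, days absent, hospitalizations, consultations and current medications from the candidates for that model, and analyze them as outcomes or cost inputs.
3. Label any model that conditions on them as a sensitivity or exploratory analysis. This includes a model using medication or diagnosis to address case mix arising from the 7:3 quota.

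The change is to wording only. It gives up some reduction in residual variance and leaves the primary model with less adjustment for case mix, which the labelled sensitivity model can examine.

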#### Dosage

To account for potential reduction of the intervention ‘dosage’ within each cluster, dosage is measured as the percentage of GPs who undergo the recovery-oriented practice training. This variable is based on the percentage of cluster staff who complete the training and remain in the cluster. For example, if two GPs at a cluster receive the training intervention at Step 1 and both remained employed at the practice/clinic/health center, this dosage variable would be 100% at Step 2.

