Estimated intervention effects will be reported as the mean outcome difference for continuous outcomes and Odds Ratio for binary outcomes between intervention and control periods, assuming a constant treatment effect over time. This can be described as a meta-analysis approach as (in the case of continuous data) the mean change in each cluster will be standardized by using the variance of the outcome measure within that cluster. The estimated intervention effects will be reported with 95% Confidence Intervals and *p* values. Analysis will be conducted using Stata V.14, StataCorp. Stata Statistical Software: Release 14. College Station, TX: StataCorp LP, 2015.

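### The multivariable primary model adjusts the intervention effect for intervention dosage, a post-randomization measure of training delivery, and the plan does not say that the model without dosage decides

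*Protocol article*

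**What the plan says.** All references are to the protocol article.

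- **Base model** (Main analysis plan): "The model will include intervention status and time as fixed effects and clusters and patients as random effects".
- **Covariates** (same paragraph): "Both univariate and multivariable models will be developed based on baseline patient and cluster-level variables", chosen at p < 0.10 or for clinical importance and entered as fixed effects. The next sentence reads "This will include the intervention dosage variable described earlier". Fit is then compared by AIC.
- **Definition of dosage** (Dosage): "dosage is measured as the percentage of GPs who undergo the recovery-oriented practice training". The next sentence changes the denominator: "This variable is based on the percentage of cluster staff who complete the training and remain in the cluster". The worked example has two trained GPs who both stay, and then "this dosage variable would be 100% at Step 2".
- **Intervention status** (Table 2): a 0/1 variable with an anticipated six-month lag. "The intervention status variable indicates that this lag time has passed".
- **Reported effect** (Main analysis plan): for continuous outcomes, a mean outcome difference "between intervention and control periods, assuming a constant treatment effect over time".

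Table 2 lists status and dosage as separate cluster-level variables for the same multivariable analysis. Nowhere is dosage confined to a dose-response analysis, an interaction, or a substitute for status.

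**The concern.** Dosage measures how much of the intervention a cluster received. It is 0 before training by definition and positive only afterwards, so it is part of the treatment and not a baseline characteristic. Putting it beside status splits the treatment effect over two coefficients. The status coefficient then compares intervention and control periods at equal dosage. Control periods before training have dosage 0, so this means a trained cluster in which nobody counts as trained.

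The plan promises one number, the mean difference between intervention and control periods, and does not say which model supplies it. If the dosage-adjusted status coefficient is the one reported, the primary result answers a different question and is usually much less precise. AIC does not settle the choice: it ranks fit and does not identify which coefficient is the intervention effect.

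**Working it through.** **Inputs from the article.** QPR SD 16, ICC 0.05, power 0.80, alpha 0.05 (taken as two-sided), two steps, three cross-sectional time points, 10 patients per GP per time point (Sample size targets); 18 clusters (Overall design); 30 GPs (Adaptations to GP recruitment and retention).

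**Assumptions.** Clusters split 9 + 9; status patterns 0-1-1 and 0-0-1; status and dosage switch on in the same period in the planned three-period dataset. The article gives no achieved dosage, so a range is used.

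**Method.** Generalized least squares for the stepped-wedge model with a random cluster intercept. The covariance of the estimates is [Σ X′V⁻¹X]⁻¹, summed over clusters, with V = (σ²(1−ρ)/m)·I + σ²ρ·J. Here σ² = 256 and σ²ρ = 12.8. With m = 10, σ²(1−ρ)/m = 24.32.

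**1. The plan's own figure.** 20 clusters × 30 patients = 600, as stated. No numeric target difference is given, so the sample size cannot be rebuilt from one. Solving for the detectable difference at 80% power gives:
- 20 clusters × 10 per period: 6.9 points (0.43 SD);
- 10 clusters × 20 per period: 7.2 points (0.45 SD);
- 10 clusters × 10 per period: 9.8 points (0.61 SD).

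This agrees with the article's verbal description of the detectable effect, so the set-up is a fair basis for the comparison.

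**2. Status effect without dosage** (18 clusters, m = 10). With K = 18 and T = 3, the status pattern gives U = 27, W = 0² + 9² + 18² = 405 and V₂ = 9×2² + 9×1² = 45.

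Variance = K·24.32·(24.32 + 3×12.8) / [(KU − W)·24.32 + (U² + KTU − TW − KV₂)·12.8]
= 18×24.32×62.72 / (81×24.32 + 162×12.8)
= 27,456 / 4,043.5 = 6.79.

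SE = 2.61. The detectable difference is 2.80 × 2.61 = 7.3 points (0.46 SD). Power for an 8-point effect (0.5 SD) is 87%.

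**3. Status effect with dosage added** (column = cluster dosage × status). Power is for an 8-point effect that does not depend on dosage.

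| Assumed dosage in trained clusters | SE of status | Ratio to 2.61 | Power |
|---|---|---|---|
| All 100% | not estimable (columns identical) | – | – |
| Spread 80–100% | 16.5 | 6.3 | 7% |
| One in nine at 50%, rest 100% | 7.5 | 2.9 | 19% |
| Spread 50–100% | 6.0 | 2.3 | 26% |
| Spread 10–100% | 3.4 | 1.3 | 65% |

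**4. A larger cluster-period size.** 30 GPs × 10 / 18 sites = 16.7. The SE without dosage is 2.07. With dosage it is 4.9 (50–100%, ratio 2.4) or 2.7 (10–100%, ratio 1.3). Mixed patterns with 60 to 80% of trained clusters at 100% and the rest at 0 to 67% give 3.2 to 4.8 (ratios 1.5 to 2.3).

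**5. What the coefficient estimates.** If the true effect is 8 × dosage, a model with status θ and dosage γ is satisfied exactly by θ = 0 and γ = 8, so the expected status coefficient is 0. Without dosage in the model, status recovers 8 × mean dosage: 7.2, 6.0 and 4.4 for mean dosages of 0.90, 0.75 and 0.55. If the effect does not depend on dosage, the status coefficient has expectation 8 either way and only its SE suffers.

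**6. All-data dataset.** Dosage changes at training and status after the six-month lag, so surveys within the lag have status 0 and positive dosage. In an illustrative monthly layout (24 months, linear time, training at months 3 and 12, dosage 100% from training), the status SE was 2.23 with and without dosage. With dosage included, the status coefficient was 8 of 8 points if the whole effect came after the lag, 4 if half did, and 0 if the effect began at training. Without dosage the values were 8.0, 4.06 and 0.11, so in this layout dosage changed little.

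**The case against.** The strongest reply is that a model with only status and time is stated first, and its status coefficient is unaffected by dosage. That is right. A reader might infer that the trial's reported effect will be stripped of the training effect; the article does not support this, because the dosage-adjusted model is one of several planned. What stands is that no sentence makes the base model decisive.

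A reader might also infer that dosage is near 100% in every trained cluster. That comes from a single conditional example. With cluster staff as the denominator it could be much lower, and a wide spread brings the SE ratio down to about 1.3. The coefficient is still an extrapolation to 0% dosage.

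The zero expectation follows only from an effect exactly proportional to dosage. If every trained cluster is at 100%, the two terms are aliased: software drops one and the other carries the whole effect, so nothing is removed.

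The lag is a fair point for the all-data dataset, where the interval need not widen. If effects start only after the lag, as Table 2 anticipates, status there keeps the whole effect.

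Finally, the intervention effect can be recovered from the joint model. The contrast of status plus dosage at mean dosage has the same SE as the model without dosage (2.61 with 10 per cluster-period, 2.07 with 16.7). The harm arises if the uncentred status coefficient is reported alone. The article specifies neither, so this limits the damage but does not remove the fault.

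**Conclusion.** The point holds in a bounded form. The article puts a post-randomization measure of training delivery into the multivariable primary model beside intervention status, describes the covariates as baseline variables, and leaves open which model decides. The secondary models are described as similar, so they inherit the problem.

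In the planned three-period dataset, the dosage-adjusted status coefficient is not the promised mean difference. It is not estimable if all trained clusters are at 100%. Otherwise its SE is about 1.3 to 2.4 times larger under most of the dosage spreads tried, and 2.9 to 6.3 times larger when dosage is tightly clustered. Its expectation is 0 only under proportionality. In the all-data dataset the two terms can separate, and status then measures the change after the lag.

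These sizes rest on a 9 + 9 split, 10 or 16.7 patients per cluster-period, and assumed dosage spreads. That the coefficient changes meaning does not depend on those figures. The change from GPs to cluster staff in the definition of dosage is a smaller, separate inconsistency.

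**What to change.** 1. State that the primary analysis is the model without dosage: intervention status and time, with any adjustment limited to true baseline covariates.
2. Remove dosage from the covariates of the primary and secondary effect models.
3. Keep dosage for a supportive analysis, labelled as dose-response, in which it replaces intervention status.
4. Give dosage one denominator and use it throughout, for example the participating GPs of the cluster, counting those who were trained and are still there.

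The cost is a sentence or two in the analysis plan and one in the dosage definition. No new data are needed, and power for the intervention effect is not reduced.
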